# Termination and Subsequent Treatment

## Premature termination of subjects / discontinuation / withdrawal

For the following reasons the patient may be taken out of the trial:

- personal wish of the participant
- withdrawal of consent
- loss of contact, move
- newly manifested exclusion criteria
- repeated adverse events
- serious adverse event
- significant violations of protocol

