| **Zielgrößen** | Primäre Zielparameter:   - Reduktion von psychotischen Positiv- und Negativ-Symptomen in SANS und SAPS-Score, - Depressivität (Calgary Depression Scale), - Psychosoziale Funktion (global assessment of functioning, GAF)   Sekundäre Zielparameter:   - Patientenzufriedenheit (Fragebogen für Zufriedenheit mit der stationären Behandlung (ZUF-8) - Lebensqualität (Modular System for Quality of Life) - Selbstwirksamkeitserwartung (Fragebogen zu Kompetenz und Kontrollüberzeugungen) - Mentalisierungsfunktionen (ToM: Reading the Mind in the Eyes Test); Gewahrsein von Emotionen in sozialen Situationen: Levels of Emotional Awareness Scale (LEAS)) |
| **Sicherheit** | Abfrage und Dokumentation unerwünschter Ereignisse zu jeder Visite. Im stationären Verlauf kontinuierliche Beurteilung und Dokumentation der Symptomschwere und etwaiger unerwünschter Ereignisse. Die Teilnehmer werden weiterhin aufgefordert, sich bei Auftreten von unerwünschten Ereignissen zwischen den Visiten umgehend zu melden. |
| **Abbruchkriterien** | Im Einzelfall:   - Suizidalität - Exacerbation der psychotischen Störung - Fremdgefährdung - Neuauftreten von Ausschlusskriterien - Unterbringungsbedürftigkeit nach dem PsychKG.   Insgesamt:  Sollten mehrere Patienten durch die Behandlung destabilisiert werden, und Suizide, Exacerbationen, Gewalt oder Unterbringungen nach dem PsychKG vermehrt auftreten, so kann die Studienleitung über den Abbruch der Studien entscheiden. |
| **Statistische Auswertung** | Die statistische Analyse in Bezug auf die Outcome-  Parameter soll mit Hilfe von T-Tests, ANCOVA und MANCOVA mit Meßwiederholung als Intention-to-treat-Analyse vorgenommen werden, wobei ausscheidende Studienprobanden in die Endanalyse einbezogen werden und die Gründe für das Ausscheiden angegeben werden. |
| **Präklinische Untersuchungen** | Ohne Relevanz |

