## Exclusion Criteria

- Organic brain disorder
- Any other psychiatric disorder apart from schizophrenia according to DSM-IV- axis I
- Antisocial personality disorder asccording to DSM-IV
- Relevant somatic disorder imparing cerebral function
- Relevant abuse alcohol and illegal drugs (urine drug screen)
- Inability to understand and comply with the requirements of the study and to give written informed consent
- Inability to participate in a group psychotherapy setting:
  - massive agitation, hostility oder aggression
  - severe impulsiveness
  - severe paranoid ideation
- Current endangerment of others
- Current suicidal intent or massive tendency to self-harm
- Hospitalisation according to Berlin Mental Health Law (PsychKG)

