## Procedures in case of emergency

In case of an exacerbation of symptoms or severe adverse reactions associated with the study intervention, emergency measures can be taken at any time by the treating psychiatrist, the psychiatrist in charge and senior physicians of the hospital. Symptoms associated with the study intervention may comprise suicidal intention, self-harm, endangerment of others, material damage, increase in psychotic symptoms like desorganisation, delusions, hallucinations, psychomotor agitation or stupor, affective tension, anxiety or perplexity, increase in depressive symptoms, etc.

Should critical situations arise during an art therapy session, nursing staff can immediately assist. The patient may like to finish the session and should be accompanied back to the ward. In case of severe adverse reactions, the intervention has to be discontinued immediately. The treating psychiatrist or psychiatrist in charge will be informed in any case and has to decide about further necessary measures. The treating psychiatrist will also decide about the patient's ability to continue study participation in cooperation with the principal investigator of the study. All adverse and serious adverse events are documented in the case report file and reported to the principal investigator within 24 hours.

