### Definition of Population for Analysis

The intent to treat analysis will be executed with all available patient’s data independent of dropouts and protocol violations. The per protocol analysis will be accepted only for the patients who finished the trial in accordance with the study protocol (valid cases).

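### Section 8.1 lets patients leave the trial for events that overlap with poor primary outcomes, and nothing says their week-6 and week-12 ratings continue

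*Protocol*

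**What the plan says.** Section 8.1 has one heading for premature termination, discontinuation and withdrawal, and one consequence: "For the following reasons the patient may be taken out of the trial". Besides the patient's wish, withdrawn consent and loss of contact, the reasons include "newly manifested exclusion criteria", "repeated adverse events", "serious adverse event" and significant protocol violations. The exclusion criteria in 4.2 that could newly arise include "severe paranoid ideation", massive agitation or hostility, suicidal intent and hospitalisation under the mental health law. The synopsis has its own list of individual stopping criteria. It names suicidality and "Exacerbation der psychotischen Störung", and does not say whether the sessions or the trial participation stops.

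Section 5.4 does distinguish two steps. After a severe reaction the intervention stops at once; the treating psychiatrist then decides on the patient's "ability to continue study participation in cooperation with the principal investigator of the study".

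On the analysis side, 13.2.2 promises an intention-to-treat analysis of all available data "independent of dropouts and protocol violations". The synopsis says that patients who leave enter the final analysis and that their reasons are reported. Table 1 and 13.2.3 place the post-baseline primary ratings (SAPS, SANS, CDSS, GAF) at week 6 and week 12 only. Section 8.3, on follow-up after premature termination, deals with treatment and aftercare and names no study assessment.

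**The concern.** The reasons for removal are not independent of the outcome. A patient with new severe paranoia would be expected to score high on SAPS. One with suicidal intent would be expected to score high on CDSS and low on GAF. Under 9.1, clinically significant worsening of an existing condition is itself an adverse event. If such a patient leaves before week 6, there is no later primary rating, and an analysis of available data cannot supply one.

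The loss could also be uneven. Section 5.4 is written around reactions to the intervention and crises during sessions, and the decision on participation follows from these. Control patients have no sessions. Section 5.5 states that the raters are blind but makes no such statement for the treating psychiatrist, who would learn the allocation when told of a session crisis. If more poorly doing patients leave the art-therapy arm, the efficacy comparison is biased towards art therapy. Section 13.1 says that the pilot is run to estimate effect sizes for a larger trial, so the bias would carry into that trial's planning.

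**Working it through.** The protocol gives no sample-size or attrition calculation, so there is no stated figure to reproduce. The check has two parts.

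**1. The text, side by side.**
- 8.1: discontinuation and withdrawal both mean leaving the trial, at the team's discretion.
- 5.4: stopping the intervention and ending participation are separate steps, but it is not said that ratings go on after either.
- 8.3: aftercare only.
- Table 1 and 13.2.3: ratings at weeks 6 and 12, with no early-termination visit.
- 13.2.2 and synopsis: dropouts and protocol violators are to be analysed.

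The last item needs data that the first four do not secure.

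**2. Size, for illustration only.** Inputs from the protocol: at least 15 patients per arm (3.1) and two-sided alpha of 0.05 (13.2.3). Assumptions: standard normal outcome with higher meaning worse, no true effect, removal before week 6, and removal in the art-therapy arm only unless stated. The removal rate is assumed. The only related figure is about 10% deterioration in psychotherapy generally (7.1), which is not a forecast for this trial.

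*Large-sample shift when the worst fraction f is unobserved:* φ(z₁₋f)/(1 − f).
- f = 10%: 0.1755/0.90 = 0.195 SD
- f = 20%: 0.280/0.80 = 0.350 SD

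*Simulation, 15 per arm, 100,000 replicates, t-test.* The k art-therapy patients with the worst trigger score are unobserved; the trigger has correlation ρ with the outcome. Cells show the shift in favour of art therapy in SD, then the two-sided type I error.

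| k removed | ρ = 1.0 | ρ = 0.7 | ρ = 0.5 |
|---|---|---|---|
| 0 | 0.00; 0.050 | 0.00; 0.050 | 0.00; 0.050 |
| 1 | 0.125; 0.073 | 0.086; 0.060 | 0.061; 0.055 |
| 2 | 0.231; 0.109 | 0.158; 0.076 | 0.115; 0.065 |
| 3 | 0.329; 0.158 | 0.229; 0.096 | 0.164; 0.072 |

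With two removed from each arm the mean bias is about 0. The type I error is then 0.085 at ρ = 1.0 and 0.056 at ρ = 0.5.

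*Masked harm.* If 10% of art-therapy patients worsen by an assumed 2 SD and all are removed, the true mean harm is 0.10 × 2 = 0.20 SD and the observed difference is 0.00.

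*Scale.* The standard error of the difference with 15 per arm is √(2/15) = 0.365 SD. A shift of 0.061 to 0.164 SD is therefore 0.17 to 0.45 standard errors.

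**The case against.** Much can be said for the protocol, and several stronger readings do not stand.

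- A reader might infer that the worst outcomes are never measured. Removal in 8.1 is permissive, every patient has a baseline rating, and anyone removed after week 6 keeps the week-6 rating. The text supports only that later ratings need not be taken.
- A reader might infer that the protocol makes no distinction between stopping sessions and ending participation. Section 5.4 makes it. What is missing is a statement that ratings continue.
- A reader might infer that harm would vanish from the record. Section 9 requires all reported adverse events to enter the analysis and 9.6 requires follow-up until they have disappeared; the synopsis requires reasons for leaving to be reported. Harm would remain visible there. However, the safety set in 13.2.4 is limited to patients with at least one art-therapy session, so this does not restore a comparison between arms.
- A reader might take 0.35 SD as the expected bias. It is a one-arm case with perfect tracking and an assumed 20% rate. The 8.1 reasons apply to both arms, and some triggers, such as a somatic serious adverse event, need not reflect psychiatric outcome. Uneven loss is plausible but not shown.
- The two lists differ little. Most synopsis criteria are also exclusion criteria, and exacerbation fits the adverse-event definition. Still, 8.1 asks for repeated or serious events, whereas the synopsis names exacerbation without that condition.
- This is a pilot without a power claim. That lowers the stakes for the test, but not for the effect-size estimate.

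The gap itself stands: no section secures the ratings that the intention-to-treat clauses presuppose.

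**Conclusion.** The point holds in limited form. The protocol permits loss of primary ratings for reasons linked to the outcome, plans no visit to prevent it, and at the same time promises an analysis that includes those patients. Analysis methods cannot recover ratings that were not taken, so the remedy belongs in the protocol.

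The size is uncertain. If one to three of 15 art-therapy patients and no controls leave before week 6, the bias is about 0.06 to 0.16 SD at a trigger-outcome correlation of 0.5 and 0.125 to 0.329 SD at a correlation of 1.0. It is about zero on average if loss is equal. At the moderate correlation this is smaller than the sampling error, but it is systematic and would favour art therapy. All of it rests on assumed removal rates, normal scores and loss before week 6. The documents do not show that such losses will occur or that they will be uneven.

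**What to change.** In 8.1, separate the end of the sessions from the end of data collection:
- State that the listed reasons may end the art-therapy sessions, while the scheduled blinded Visit 2 and Visit 3 ratings continue for all randomised patients, who stay in the intention-to-treat analysis.
- Allow three exceptions: consent to assessment is withdrawn, contact is lost, or the patient can no longer give valid consent to assessment. The third is needed because inability to consent is an exclusion criterion (4.2) and 4.3 bars patients who cannot consent.
- Do not use protocol violations as a reason to end ratings.
- Time Visit 2 by the planned six-week period. Table 1 ties it to the end of the intervention, which is ambiguous for a patient who stops early.
- Record the date and reason for stopping sessions and, separately, for ending ratings.
- Reconcile the lists in the synopsis and 8.1, and say in both what is being stopped. The clinical criteria are not at issue and need not change.

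The cost is protocol wording. The visits are already scheduled and none is added. Some ratings of unwell patients will be harder to obtain. In the simulation, with no rating lost, the bias is 0.00 SD and the type I error 0.050.

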## Premature termination of trial

For the following reasons the trial may be terminated prematurely:

- decision of the PI with regard to a new risk-benefit-evaluation (e.g. occurrence of non-justifiable risks)
- new scientific findings which do not justify further continuation
- non-sufficient recruitment

The decision about premature trial termination will be made by the principal investigators.

## Follow up procedures and continuing medical care after (premature) termination

No particular scheme is recommended for treatment after the 12 weeks treatment period. Study participation will not have any influence on aftercare. All patients will receive standard treatment.

# Adverse Events

All adverse events reported during the study must be included in the analysis.

## Definition of Adverse Events (AE) concerning the trial

An adverse event is any untoward medical occurrence in a patient or clinical trial subject administered a medicinal product/intervention and which does not necessarily have a causal relationship with this treatment (according to Directive 2001/20/EC).

An AE can therefore be any unfavourable and unintended sign (including abnormal laboratory finding), symptom, or disease temporally associated with the use of a medicinal (investigational) product/intervention, whether or not considered related to the medicinal (investigational) product/intervention.

AEs also include: any worsening (i.e. any clinically significant change in frequency and/or intensity) of a pre-existing condition that is temporally associated with the use of the study drug/intervention; abnormal laboratory findings considered by the reporting investigator to be clinically significant; and any untoward medical occurrence.

## Definition of Serious Adverse Events (SAE) concerning the trial

A serious adverse event is any untoward medical occurrence or effect that at any dose results in death, is life-threatening, requires hospitalisation or prolongation of existing hospitalisation, results in persistent or significant disability or incapacity, or is a congenital anomaly or birth defect (according to Directive 2001/20/EC).

## Definition of Suspected Unexpected Serious Adverse Reactions (SUSAR) concerning the trial

A Suspected Unexpected Serious Adverse Reaction (SUSAR) is an adverse event, the nature or severity of which is not consistent with the applicable product information, i.e. “expected” AE.

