| **Mögliche Risiken, Kontraindikationen, Maßnahmen, die bei eventuellen Zwischenfällen zu ergreifen sind** | Mögliche Risiken:   - Durch die Bearbeitung von Ängsten, inneren Konflikten oder paranoid belegten Themen während der therapeutischen Intervention könnte es zu einer temporären Destabilisierung des Patienten mit steigender Dynamik von Wahn, Halluzinationen und formalen Denkstörungen oder Depressivität kommen. - In einzelnen Fällen könnte die Gefahr von Fehlverhalten mit Gefährdung des Patienten selbst oder Dritter ebenfalls zunehmen. Mögliche Nebenwirkungen/ Komplikationen wären dann: Suizidalität, Suizidversuche, Suizid und Aggressivität.   Kontraindikationen: siehe Ausschlusskriterien (auch Neuauftreten von Ausschlusskriterien)  Maßnahmen, die bei eventuellen Zwischenfällen zu  ergreifen sind:   - Deeskalierende und stützende Intervention durch den Kunsttherapeuten. In der Regel sollte die Therapieeinheit nach einem Krisengespräch und eventuell einer kurzen Pause mit allen Teilnehmern zu Ende geführt werden. Bei schweren Erregungszuständen muss die Therapieeinheit für den betroffenen Patienten abgebrochen werden. In diesem Fall sowie bei Verdacht auf Suizidalität oder Eigen- und Fremdgefährdung muss der behandelnde Arzt sowie der Studienarzt informiert werden. Geeignete Schutzmaßnahmen werden durch den Arzt eingeleitet. |
| Risiko-Nutzen-Abwägung | Die Kunsttherapie birgt aller Erfahrung nach für die Teilnehmer  nur geringe Risiken, und diese können im stationären  Behandlungsrahmen minimiert werden. Sollte es zu Steigerung  ängstlicher Erregung, Anspannung oder Feindseligkeit und Aggressivität kommen, so wäre der Therapeut zu einer geeigneten Deeskalation in der Lage und könnte jederzeit umgehend auf ärztliche Hilfe zurückgreifen, wenn dies notwendig sein sollte. Bei geringer Gruppengröße und  erfahrenen Gruppenleitern sollte in den meisten Fällen ein  erfolgreiches deeskalierendes Eingreifen möglich sein. Der zu  erwartende Nutzen der Intervention überwiegt bei weitem die  Risiken. Ärztliche Hilfe und Hilfe von Krankenpflegekräften steht auf der Station ständig zur Verfügung. |

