### Side effects and possible adverse events

The processing of anxiety, inner conflict or topics linked to paranoid ideation during therapeutic intervention could lead to a temporary destabilization of the patient with increasing dynamics of delusions, hallucinations and formal thought disorder or depression. Possible side effects/ complications would be exacerbation of psychotic symptoms, suicidal ideation, suicide attempts, suicide and aggression.

Adverse effects may also result from the treatment in a group setting. Hoffmann et al. therefore created a list of indications and contraindications for group psychotherapy (see also [24] and [25]). Participants should be able to adhere to the framework agreements (such as dates, duration). Psychotic symptoms of other patients might impose a burden on participants, and problems may arise from unfavourable group dynamics that might not always be resolved by the therapist. However, the specific technique of art therapy as well as the inpatient setting are suitable to recognise and minimise risks. Art therapy is less demanding with respect to the mental stability of patients compared to other group therapies, because it allows for a unique triadic interaction between patient, therapist and work of art. Art therapy offers a creative space that can bear protective properties. A lot of time is spent working silently, and adverse tendencies in group dynamics can be effectively controlled by the therapist. However, individual adverse reactions to the group setting or as a result of high emotional intensities evoked by self-exploration in the creative process can not be completely excluded.

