# Risk-Benefit-Analysis

## Risks, side-effects, strains, advantages and disadvantages

Under ethical considerations, the study follows strictly an ‘add-on’ approach. All patients receive the usual standard treatment including pharmacotherapy and any other indicated psychological or adjunctive therapy. The overall amount of adjunctive treatment sessions can be adapted in the control group by participation in additional sessions of occupational or other therapies.

There are no systematic reports on the possible risks and adverse effects of art therapy in general or for its use in the treatment of schizophrenia. In contrast, adverse effects and risks of (group) psychotherapy have been focused increasingly in recent years. Hoffmann et al. 2008 [13] conclude that group dynamic processes may yield negative effects for individual participants. As earls as in the 1960ies, Bergin et al. [13] demonstrated deteriorations of health in about 10% of patients who underwent psychotherapy. According to Margraf et al. [16] three causal categories may be responsible for adverse reactions associated with the psychotherapeutic process:

1. failure or adverse effect of an adequate therapy

2. failure or adverse effect of an inadequate, unprofessionally conducted treatment

3. mismatch between personalities of patient and therapist.

Group therapies might endanger patients if groups are too large, if therapies have a too strongly disclosing/interpreting character and if confrontations between participants are not limited. Also, wrong indication and lack of guidance may increase the risk of adverse reactions [15]. Negative socio-dynamic processes like rivalry, aggression, submission or withdrawal that are not sufficiently contained and resolved by the therapist may have an unfavorable impact on individual patients.

However, despite of potential risks, group therapies are a broadly used and essential means of hospital and outpatient treatment.

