## Reporting of Serious Adverse Events (SAE) and Suspected Unexpected Serious Adverse Reactions (SUSAR)

**SAE:**

All serious adverse events will be reported immediately to the sponsor by the investigators according to GCP-V § 12. SAE which need not be reported: surgeries or other inpatient residences known *before* inclusion in the trial. Serious adverse events which occur after conclusion of the study and can still reasonably be considered to be related to the study intervention are also to be reported. Any death during the study has to be reported to the sponsor within 24 hours. In cases where a pathologist's report may substantially assist in clarifying the event an autopsy should be performed. In addition biopsy materials, blood samples and specialist's reports should be provided if considered useful.

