**SUSAR:**

The sponsor must report all suspected serious unexpected adverse reactions occurring during the course of the study to the Ethics Committee, Competent Authority (if applicable) and investigators within 15 days, according to GCP-V § 13. In case of death, the SUSAR has to be reported within 7 days, and further relevant information has to be provided within the next 8 days.

All transferred data have to be pseudonym. Reporting of SUSARs require unblinding of the individual.

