## Monitoring

There will be no external monitoring for this pilot study.

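### Section 9.3 judges whether a serious reaction is unexpected against product information that art therapy does not have, so the protocol leaves open whether a related suicide must be reported to the ethics committee

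*Protocol*

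**What the plan says.** Section 9.3 says that a SUSAR "is an adverse event, the nature or severity of which is not consistent with the applicable product information". The sentence then closes by pointing to the expected category, although it is defining the unexpected one. Its body mentions neither seriousness nor a suspected causal link.

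Section 7.1 states: "There are no systematic reports on the possible risks and adverse effects of art therapy in general". No section names an investigator's brochure, a reference list or any other document for judging expectedness.

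Section 5.1.1, on side effects, says: "Possible side effects/ complications would be exacerbation of psychotic symptoms, suicidal ideation, suicide attempts, suicide and aggression". The German synopsis gives a matching list under possible side effects and complications: "Suizidalität, Suizidversuche, Suizid und Aggressivität".

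On reporting, section 9.7 says: "All serious adverse events will be reported immediately to the sponsor by the investigators". It requires deaths to be reported to the sponsor within 24 hours. Section 5.4 sends adverse and serious adverse events to the principal investigator within 24 hours. For the ethics committee, 9.7 says: "The sponsor must report all suspected serious unexpected adverse reactions occurring during the course of the study to the Ethics Committee". The limit is 15 days, or 7 days for a fatal SUSAR.

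**The concern.** The definition is drug-trial wording applied to a psychotherapy. An investigator who has to decide whether a serious related event is unexpected is sent to a document that does not exist. The nearest thing in the protocol is its own list of foreseen harms, and that list includes the gravest event the trial could see. Whether the list is used as the reference decides whether the ethics committee hears of such an event promptly.

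Little else in the protocol would bring the event to an outside body. Section 11.1 states: "There will be no external monitoring for this pilot study". Section 13.2.5 plans no interim analysis, and section 8.2 leaves early termination to the principal investigators. Section 3 makes preliminary safety data a purpose of the pilot, so the rule for serious related harm should be one that can be applied.

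**Working it through.** No arithmetic applies. The check sets the definitions beside the reporting duties and follows one event through them.

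**Elements of the definition**

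| Element | Section 9.3, heading and term | Section 9.3, defining sentence | Section 9.7, reporting duty |
|---|---|---|---|
| Serious | yes | absent | yes |
| Suspected causal link | yes | absent | yes |
| Unexpected | yes | yes, against product information | yes, no reference given |
| Reference that exists for art therapy | none named | none named | none named |

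The heading and 9.7 supply the first two elements that the sentence lacks. Nothing supplies the reference.

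**A suicide judged related to the intervention**

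1. It results in death, so it is a serious adverse event under 9.2.
2. It goes to the sponsor within 24 hours (9.7) and to the principal investigator within 24 hours (5.4).
3. Expectedness must now be judged under 9.3, and there are two ways to do so:
   - Reading A: the risk list in 5.1.1 and the synopsis stands in for product information. Suicide is on the list, so it is expected and not a SUSAR. Section 9.7 requires no ethics committee report.
   - Reading B: no reference exists, so nothing is expected. The death is a SUSAR and is due at the ethics committee within 7 days.
4. No section chooses between A and B.

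**Other routes to the ethics committee.** Section 15.1.1 concerns approval of the protocol and related documents. Section 15.1.4 tells patients that their data might be passed to the ethics committee. Neither creates a duty to report an event. The 7-day rule for deaths in 9.7 applies only to a death already classed as a SUSAR, so it does not settle step 3.

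**Other listed harms.** A related suicide attempt that is life-threatening, or that requires or prolongs hospitalisation, meets 9.2 and faces the same choice: 15 days under B, no report under A. Suicidal ideation, aggression and worsening psychosis are not serious by name under 9.2. Expectedness matters for them only when a seriousness criterion is met.

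**Which events count as suspected.** Section 9.5 has five causality grades: unassessable, unlikely, possible, probable and certain. The possible grade includes events that the patient's clinical state could readily have produced. Neither 9.3 nor 9.7 says which grades make a reaction suspected.

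**The case against.** The strongest reply is that nothing makes 5.1.1 the expectedness reference. That section is written conditionally. Section 9.3 tests against product information, not against a discussion of risks, and section 7.1 says that clinical use has shown no sign of adverse effects. On that view Reading B is the natural one, and a related suicide is reported within 7 days. This stands in part: the protocol does not oblige anyone to call suicide expected. But B is an inference too, and a rule for the most serious event should not depend on it.

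A reader might infer from the bare sentence in 9.3 that every mild, unrelated event becomes a SUSAR, and that outcome raters are then unblinded for trivial events. The document does not support this. The heading and the defined term contain suspected and serious, 9.2 defines serious just before, and 9.7 repeats both words. Section 9.7 requires unblinding of the individual for a SUSAR report but does not say that the raters are told, and section 5.5 allows unblinding of raters only for safety reasons. The gap in 9.3 is a drafting mismatch to be aligned.

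A reader might also infer that all five harms named in 5.1.1 lose reporting. They do not, because several are serious only in some cases.

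Finally, section 9.7 cites GCP-V, and section 15.1 cites ICH GCP and local law. These may impose reporting duties beyond the protocol's text. That cannot be checked from the document, so it would be too strong to say that such a death would never reach the ethics committee. The synopsis also lets the trial leadership stop the trial if suicides, exacerbations, violence or committals become more frequent, but that is an internal decision and not a report.

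**Conclusion.** The point holds as a defect in a safety rule. The expectedness test in 9.3 cannot be applied as written because its reference does not exist for this intervention, and its sentence does not match the duty in 9.7. For a related suicide, the outcome under the protocol's own text is either a report within 7 days or no required report to the ethics committee. The same uncertainty covers any other listed harm that meets 9.2 and is judged related.

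This rests on two conditions. First, no reference safety document exists outside the protocol; none is named. Second, the statement that no report is required refers to the protocol's text alone and not to the legislation it cites. Endpoints and the efficacy analysis are unaffected. The change is worth making before recruitment, because SUSAR definition and reporting belong in the protocol and are not matters for a later analysis plan.

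**What to change.** Rewrite section 9.3 along these lines:

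*A SUSAR is a serious adverse event (section 9.2) that is suspected to be related to the study intervention and is unexpected. An event counts as suspected if its causality under section 9.5 is graded [categories to be listed]. No reference safety information exists for art therapy. The theoretical risks described in section 5.1.1 and in the synopsis do not make an event expected. Serious adverse events suspected to be related are therefore reported to the ethics committee under section 9.7.*

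Delete the reference to product information and the closing clause about the expected category, and use the same term in 9.3 and 9.7. The investigators need to choose the causality categories. Including the possible grade would bring in more events, because it covers events that the underlying illness could readily explain.

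An alternative is to adopt a named list of expected events. The protocol would then have to say explicitly how serious related events on that list, deaths included, reach the ethics committee.

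The cost is a few sentences and some additional ethics committee reports. Their number cannot be derived from the document. In acutely ill inpatients a prolonged stay is already a serious event under 9.2, so it need not be negligible, but the trial has only about 30 patients.
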